#### Immigrant families

The questionnaire aimed at families from countries of sub-Saharan Africa in which FGM is present and who use the healthcare centres will be given to the group of men and women of the community who, through the intervention of cultural mediators, agree to participate in the study and who have been directly or indirectly in contact with the problem. In this part of the study we cannot perform a randomised or systematic sample, since no randomisation list is available, but rather we must base the sample on criteria of accessibility (temporal, idiomatic, cultural, opportunity, etc.) to these mediators to at least allow determination of the point of view of the persons affected from the community, previously assuming the possibility of introducing a certain bias in selection. A convenience sample will be made according to attendance to the healthcare centre and fulfilment of the inclusion criteria: to be a legal resident in Spain during the last year, be over the age of 18 years, attend the primary care centre for any reason and be from any of the countries in which FGM is practised. Two cultural mediators from the community (Senegal and Gambia) who have undertaken specific training in intercultural mediation and who usually provide such mediatory support to the PHC will participate in these surveys. They will receive specific instruction regarding the objectives of the study, the content of the questionnaires and the clarifications or explanations which may be given to the participants. Prior to beginning the field work, 3 to 6 simulated interviews will be performed in the presence of one of the members of the investigative team. The work of the mediators will be fundamentally based on introducing the interviewers and accompanying them throughout the whole interview process to clarify any concept or doubt which may emerge during the interview. Translation will also be provided by these mediators, if necessary.

Informed consent will be requested from participants in the study. In the case of migrant people, cultural mediators may be required to obtain this informed consent.

Sample size: According to the last municipal registry data available (11% of the immigrant population, 13.5% of which is of sub-Saharan origin), the population eligible in our study area is of 7,200 individuals. We assume that the prevalence of FGM in most of these countries is above 80% according to the reports of international organisations [6]. With an alpha risk of 0.05% for a precision of ± 0.06 percentual units and assuming 10% of non-responders, a sample of 191 subjects is required.

Non responders: a questionnaire will be elaborated for the immigrants selected who refuse to participate in the study. This questionnaire will collect only sociodemographic data, country of origin, etnia, years of residence in Spain and the reason for refusal to participate as well as the name of the person who proposed their participation in the study (interviewer, mediator or both). The aim of this questionnaire is to identify differences between the responder and non responder immigrant populations.

With respect to the healthcare professionals, the different rates of participation in the Primary Healthcare Centres will be taken into account in the analysis. Thus, if necessary, the principal results will be stratified according to the rate of participation.

### Study variables

The questionnaire to the healthcare professionals will assess knowledge on FGM, attitudes and skills in approaching this problem in relation to the following areas:

• Sociodemographic data and of the professional setting: age, gender, professional category, work centre or department.

• Assessment of knowledge on: typology of FGM, cultural origin, geographic distribution and ethnicity of FGM, legal implications, consequences for the health of the women, formation received.

• Assessment of the attitudes of the professionals in relation to: beliefs regarding FGM, professional interest in relation to FGM, convenience or need to act on this problem, fears or insecurity generated on considering this subject, availability of preventive interventions, negativity towards immigrant patients, attitude toward judicial interventions related to FGM and their implications.

• Agreement or disagreement of the professional towards the response or actions to be undertaken in a situation of risk for a girl or towards a recent FGM.

• Previous contact with cases of FGM or situations of risk and previous experiences.

Similarly, the questionnaire for the families will include the following areas:

• Sociodemographic data: age, gender, country of origin, ethnicity, years of residence in Spain, number of children. Position of the different members of the family towards FGM.

• Knowledge of the consequences which FGM may have on the health of a girl.

• Knowledge of Spanish legislation and of the country of origin regarding FGM and the consequences of its practice, experiences (acceptation or rejection) related to the criminalisation of this practice.

• Position (acceptation or rejection) towards a possible preventive action on behalf of the healthcare professionals in Spain.

• Expectations towards the proposal of a preventive intervention aimed at their communities of origin, consequences of not performing FGM in relation to the community in both the country of origin and destination (diaspora), acceptation of alternative rituals to FGM.

Sociodemographic data (age, gender, ethnicity, country of origin, years of residence in Spain and number of children) will be collected from the sub-Saharan healthcare users who do not wish to complete the questionnaire, with the aim of detecting possible differences between users who accept and refuse to participate in the study.

### Questionnaire elaboration

The questionnaires will be developed [29] in several steps described as follows:

**- 1st phase: **Different aspects related to knowledge, attitudes and practices in relation to FGM which may be determined through the questionnaire will be identified from previous experiences, the bibliography consulted and knowledge of the investigative team [14,15]. This will be carried out by the 8 professionals of the investigative team.

**- 2nd phase:, **A group of 8-10 primary care professionals will be selected with the nominal group technique and the most relevant aspects to be incorporated into the questionnaire will be proposed. The nominal group will be composed of primary healthcare professionals with experience in the approach to FGM and providing care to immigrant populations.

**- 3rd phase: **The investigative team will elaborate the questionnaire from the results obtained in the previous phases. The questionnaire to the professionals will be self-administered and the questionnaire to the families will be hetero-administered. This phase will be carried out by the 8 professionals of the investigative team.

**- 4th phase: **The questionnaire will be sent to a multidisciplinary team of primary healthcare professionals (from 20 to 30), randomly selected from the target population, to validate the content and practical aspects of presentation and comprehension of the questions. Between 15 to 20 days after having received the answers, the questionnaire will be resent to the same professionals with the aim of evaluating the stability of the scores. In the case of the families a similar procedure will be carried out with mothers or fathers of girls at an age of risk of undergoing FGM through the help of intercultural mediators.

**- 5th phase: **From the results obtained in the fourth phase, the questionnaire will be modified and the definitive version will be elaborated. This will be carried out by the professionals of the investigative team.

**- 6th phase: **The definitive questionnaire will be administered to the professionals established in the study as well as the families according to the description in the section Study Subjects. A group of responders (from 20 to 30 persons) will be selected to respond once again after 15-30 days with the aim of evaluating the stability of the responses. In the case of the families a similar procedure will be undertaken.

The validity of the construction (correlation between the operative definition of the concept and the aspects evaluated by those surveyed) and the previously described dimensions (validity of content) will be evaluated. The internal consistence of the questionnaire will be analysed with the Cronbach's alpha, both globally and for each of the dimensions. Values between 0.70 and 0.90 will be considered optimum. A factor analysis will be performed to determine the factorial structure of the questionnaire and the agreement between the theoretical dimensions proposed will be evaluated.

Stability will be measured with test-retest concordance, using the simple concordance index and the Kappa coefficient. The results of this index will be evaluated with the Fleiss criteria (< 0.40 poor concordance, 0.40 to 0.75 acceptable concordance and > 0.75 indicates good concordance).

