There are few studies in Spain related to FGM in primary care. A previous survey carried out by investigators of our team of healthcare professionals in the county of the Maresme (Barcelona) [14,15] reported that 56% of those surveyed did not correctly identify the typology of FGM, 17% were not interested in the subject and their answer to the question "What would you do in the case of FGM?" was: "ignored". Twenty-one percent of the personnel of the sexual and reproductive healthcare programme, 7% of the paediatricians and 5% of the general medicine professionals declared having detected or known of some case in both mothers and daughters. This study demonstrated the profound lack of knowledge of the healthcare professionals in relation to this subject, raising the need to sensitise and educate from the privileged setting of primary healthcare, where most of the cases or situations at risk are detected. In other European countries the situation is similar [16-18].

The important migratory waves of sub-Saharan populations to the European Union in the last years are shaping societies which are increasingly more complex and diverse. The way to deal with the health problems affecting these people represents a challenge for the healthcare systems [19] and for the professionals working within who must develop approaches to allow transcultural care [20-22].

Based on the production of mapping FGM in Spain, with data of the census and municipal registration, updated in 2005 we have estimated that 3,659 women living in Catalonia have undergone some type of FGM; and 2,189 girls are at risk of having some type of FGM performed in the next years, without taking into account the impact of the last processes of immigration regularisation.

The deep-rooted social and cultural nature of these practices conditions their perpetuation despite the development of important legal restrictive initiatives in some countries of origin and destination of the immigrants. However, when migrant women return to their societies of origin they are points of reference, credibility and recognition in such transcendent aspects as reproductive health and education [23]. These women bear new knowledge acquired in Europe which has been incorporated and put into practice during the migratory process. Thus, the exploration of the beliefs and perceptions of the sub-Saharan immigrants attending our healthcare centres in relation to FGM may be of interest.

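### With 20 to 30 retest subjects, a kappa point estimate cannot tell adjacent stability bands apart, and for rare answers kappa is often undefined or turns on one person

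*Protocol article*

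**What the plan says.** Under Questionnaire elaboration, the protocol article plans two retests. In the 4th phase the draft goes to a "multidisciplinary team of primary healthcare professionals (from 20 to 30), randomly selected from the target population", and 15 to 20 days after their answers "the questionnaire will be resent to the same professionals with the aim of evaluating the stability of the scores". In the 6th phase, on the final questionnaire, "A group of responders (from 20 to 30 persons) will be selected to respond once again after 15-30 days". For the family questionnaire, "In the case of the families a similar procedure will be undertaken", with no separate number.

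The statistics are fixed in the same section: "Stability will be measured with test-retest concordance, using the simple concordance index and the Kappa coefficient". Then: "The results of this index will be evaluated with the Fleiss criteria", with cut-offs at 0.40 and 0.75 giving poor, acceptable and good. The article gives no expected kappa, no precision target and no reason for 20 to 30.

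Between the two retests comes the 5th phase: "From the results obtained in the fourth phase, the questionnaire will be modified and the definitive version will be elaborated". No cut-off for keeping, changing or dropping an item is stated.

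The Background shows how rare some answers may be. In the team's earlier survey, 21% of the sexual and reproductive healthcare staff, and "7% of the paediatricians and 5% of the general medicine professionals declared having detected or known of some case". Previous contact with cases remains an area of the new questionnaire (Study variables) and serves the fifth objective (Analysis plan).

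**The concern.** A three-band scale read from a point estimate works only if the estimate is precise relative to the width of the bands. The middle band is 0.35 wide. If the 95% interval is about that wide on each side of the estimate, the label says little about which of two neighbouring bands an item belongs to.

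Rare answers raise a second difficulty. With 5% to 7% answering yes, a group of 20 to 30 holds about one or two such answers (20 × 0.05 = 1.0; 30 × 0.07 = 2.1). Kappa then depends on a single respondent, or cannot be computed.

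At stake is the published description of the questionnaire's stability, above all for the previous-contact items. Band labels could also be given more weight than they can bear when the draft is revised in the 5th phase.

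**Working it through.** **Plan's own figure.** The 20 to 30 has no stated derivation, so there is nothing to reproduce.

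**Inputs.** From the article: n = 20 to 30; cut-offs 0.40 and 0.75; prevalences 5%, 7% and 21%. Assumed, because the article does not give them: two-category items, kappa computed item by item, the same share p answering yes on both occasions, and the true kappa κ.

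**Step 1. Precision.** For a two-category item with equal margins, in large samples:

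Var(κ̂) = (1−κ)[(1−κ)(1−2κ) + κ(2−κ)/(2p(1−p))]/n

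Check at κ = 0.6, p = 0.5, n = 25: 0.4 × [0.4 × (−0.2) + 0.84/0.5]/25 = 0.64/25 = 0.0256, so SE = 0.16. The interval is 0.60 ± 1.96 × 0.16 = 0.29 to 0.91, which touches all three bands.

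At the centre of the middle band, κ = 0.575:

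| p | n | SE | 95% half-width |
|---|---|---|---|
| 0.5 | 20 | 0.183 | 0.36 |
| 0.5 | 30 | 0.149 | 0.29 |
| 0.8 | 20 | 0.230 | 0.45 |
| 0.8 | 30 | 0.188 | 0.37 |

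Half the middle band is 0.175, so an interval centred there runs past both cut-offs in every row. For scale, a half-width of 0.175 would need about 84 persons at p = 0.5 (1.96² × 0.669/0.175²) and about 134 at p = 0.8.

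**Step 2. How often the band is right.** 2×2 tables were simulated (at least 100,000 per setting) and classified with the article's cut-offs:

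| n | p | true κ | undefined | poor | acceptable | good |
|---|---|---|---|---|---|---|
| 25 | 0.5 | 0.2 | 0% | **85%** | 15% | 0.2% |
| 25 | 0.5 | 0.6 | 0% | 12% | **68%** | 20% |
| 25 | 0.5 | 0.8 | 0% | 0.3% | 30% | **70%** |
| 25 | 0.5 | 0.9 | 0% | 0% | 6% | **94%** |
| 20 | 0.8 | 0.575 | 0.2% | 27% | **51%** | 22% |

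Bold marks the correct band. An item whose true kappa lies on a cut-off is close to a coin toss between the two neighbours: at 0.40 and n = 20 to 30, it is called poor in about 49% to 54% of samples for p = 0.5 to 0.8.

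**Step 3. Rare answers.** Kappa is undefined when everyone gives the same answer both times. With p = 0.05 and κ = 0.8, P(no, no) = 0.95² + 0.8 × 0.05 × 0.95 = 0.9405, and 0.9405^25 = 0.216.

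| n | p | true κ | undefined | poor | acceptable | good |
|---|---|---|---|---|---|---|
| 25 | 0.05 | 0.8 | 22% | 14% | 16% | **48%** |
| 25 | 0.07 | 0.6 | 8% | 30% | **32%** | 30% |
| 25 | 0.07 | 0.8 | 11% | 12% | 21% | **55%** |
| 25 | 0.21 | 0.8 | 0.1% | 2% | 34% | **64%** |

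**Step 4. One person decides.** Take 25 pairs with one person answering yes the first time and no the second, and everyone else no twice. Observed agreement is 24/25 = 0.96, chance agreement is 0.04 × 0 + 0.96 × 1 = 0.96, and kappa is 0. If that person says yes both times, kappa is 1. One answer moves the item from the bottom to the top of the scale.

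**The case against.** Four points can be made against this.

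1. *The extremes do separate.* This stands. With balanced answers and n = 25, an item with true kappa 0.2 is called poor in 85% of samples and good in 0.2%; one with true kappa 0.9 is called good in 94% and poor practically never. A reader might infer that the plan sorts items largely by chance. The figures do not support that for balanced items; only neighbouring bands blur.

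2. *No band triggers an action.* This stands too. A reader might infer that sound items will be altered and unstable ones kept because of noise. No passage ties a kappa band to changing an item. The 6th-phase retest is done on the final version and nothing is changed after it. The 4th phase also serves to check content and comprehension.

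3. *Raw agreement is already planned.* True: the simple concordance index would expose the case of kappa 0 at 96% agreement. It does not help a reader who is given a band label for that item.

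4. *Intervals and the handling of rare answers belong in a fuller document.* As an omission alone this would be no finding. Here the article itself fixes both the group size and the scale on which the result is read, and the difficulty lies in that pairing.

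The 5% case is also the least favourable of the three Background figures. At 21%, undefined kappas almost vanish, and the problem returns to that of adjacent bands.

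**Conclusion.** The point holds in a limited form. At 20 to 30 subjects, the 95% interval for the kappa of a yes/no item near the middle band is about ±0.3 to ±0.45, so the point estimate cannot place an item in one of two adjacent bands. Clearly poor and clearly good items with balanced answers are usually placed correctly. For answers as rare as 5% to 7%, the prevalence in two of the three staff groups of the earlier survey, kappa at n = 25 is undefined in 8% to 22% of samples, and the label is right in only about 32% to 55%, in the settings shown with true kappa 0.6 or 0.8.

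This rests on two answer categories and on kappa being computed per item; the article states neither. Ordered answers with more categories could give different standard errors.

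A reader might also infer that the retest group must be enlarged. That would follow only if firm band verdicts were wanted, and the article does not say they are. The point is minor: it concerns a supporting validation step, and no main estimate in the Analysis plan depends on it.

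**What to change.** In the stability paragraph of Questionnaire elaboration:

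- Report each kappa with its 95% interval, beside the simple concordance index already planned.
- State that a band label on the point estimate is descriptive and is not on its own a reason to change an item in the 5th phase.
- For items with very few answers in one category, such as previous contact with cases, report positive and negative agreement instead of a kappa band.

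The cost is a few sentences and a few more lines of output. The downside is fewer firm labels of acceptable or good stability. No extra respondents are needed.

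### Test-retest stability is measured only by simple agreement and a kappa of unstated weighting, which understate the stability of any graded item or multi-level score

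*Protocol article*

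**What the plan says.** All the relevant text is in the protocol article under Questionnaire elaboration.

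- **Phase 4.** The draft goes to a "multidisciplinary team of primary healthcare professionals (from 20 to 30), randomly selected from the target population". After 15 to 20 days "the questionnaire will be resent to the same professionals with the aim of evaluating the stability of the scores". Families follow a similar procedure.
- **Phase 5.** "From the results obtained in the fourth phase, the questionnaire will be modified and the definitive version will be elaborated".
- **Phase 6.** After the definitive version is given, a further 20 to 30 responders "will be selected to respond once again after 15-30 days with the aim of evaluating the stability of the responses".
- **Measure.** "Stability will be measured with test-retest concordance, using the simple concordance index and the Kappa coefficient". No other stability index is named, and the text does not say whether kappa is weighted.
- **Reading.** The Fleiss criteria: "< 0.40 poor concordance, 0.40 to 0.75 acceptable concordance and > 0.75 indicates good concordance".
- **Scales.** "The internal consistence of the questionnaire will be analysed with the Cronbach's alpha, both globally and for each of the dimensions". A factor analysis is planned as well.

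**The concern.** The stated target and the stated measure do not fit well together. The target in phase 4 is scores, and computing alpha for each dimension and for the whole questionnaire treats those sets of items as scales. The measures are the simple concordance index, which credits only identical answers, and kappa, which in its unweighted form does the same after a correction for chance. On a graded item, a move from one category to the next is then penalised as heavily as a move from one end to the other. On a summed score with many levels, identical totals on two occasions are uncommon even when the score is stable.

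The fixed bands make this matter. A graded item or dimension score with high test-retest correlation can fall below 0.40 and be called poor. That label would be one of the phase 4 results available to the team in the phase 5 revision, and it would understate the stability reported from phases 4 and 6.

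**Working it through.** The article gives no stability estimate or calculation to reproduce. Its only figures here are the bands and the 20 to 30 respondents. The number of levels, the cut-points and the test-retest correlation are therefore assumptions, shown over a range.

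**Model.** Test and retest values are bivariate normal with correlation r, cut into k equally likely categories.

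**Formulas.**
- Unweighted kappa = (Po − Pe)/(1 − Pe), where Po is the probability of identical categories and Pe = 1/k.
- Quadratic-weighted kappa = 1 − D/D0, where D is the mean squared category difference between test and retest, and D0 is the same quantity under independence, (k² − 1)/6.

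**Five levels** (Pe = 0.20, D0 = 24/6 = 4)
- r = 0.80: Po = 0.467, so kappa = (0.467 − 0.20)/0.80 = 0.33, *poor*. D = 1.009, so weighted kappa = 1 − 1.009/4 = 0.75.
- r = 0.90: Po = 0.573, so kappa = 0.373/0.80 = 0.47, *acceptable*. D = 0.583, so weighted kappa = 0.85, *good*.

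**Eleven levels, as for a summed score** (Pe = 0.091, D0 = 120/6 = 20)
- r = 0.80: Po = 0.254, so kappa = 0.163/0.909 = 0.18. D = 4.455, so weighted kappa = 0.78.
- r = 0.90: Po = 0.334, so kappa = 0.243/0.909 = 0.27. D = 2.339, so weighted kappa = 0.88.

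**Formats where the effect shrinks or vanishes**
- Three levels, r = 0.80: Po = 0.649, so kappa = (0.649 − 0.333)/0.667 = 0.47, against 0.69 weighted. The expected value is in the acceptable band.
- Binary, split 50/50, r = 0.80: kappa = (2/π)·arcsin(0.80) = 0.59, with or without weights.

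**Chance that a sample of 20 to 30 falls below 0.40** (simulation from the same model)

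| Format | r | Unweighted | Quadratic-weighted |
|---|---|---|---|
| 5 levels | 0.80 | about 0.7 | at most about 0.01 |
| 5 levels | 0.90 | about 0.3 to 0.36 | about 0 |
| 11 levels | 0.90 | about 0.9 | about 0 |
| 3 levels | 0.80 | about a third | about 0.01 to 0.04 |
| Binary 50/50 | 0.80 | about 0.11 to 0.19 | same |

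**Precision.** Even the weighted index is loose at this size. For 5 levels at r = 0.80, the central 95% of sample values runs from about 0.47 to 0.90 with 20 respondents and from 0.53 to 0.88 with 30.

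**Sensitivity to cut-points.** With one skewed set of five categories at r = 0.80, unweighted kappa was 0.42 and weighted 0.70. The gap remains, but the label moves to acceptable.

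**The case against.** The strongest reply is that the problem depends on two things the article does not state.

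- **Weighting.** The text names kappa without saying it is unweighted, and an article may leave that detail to the full protocol. This stands for kappa. It does not cover the simple concordance index, which counts exact matches in any case, nor the absence of a score-level index beside a stated aim of "with the aim of evaluating the stability of the scores".
- **Response format.** No format is given, and several items under Study variables are worded as two categories (agreement or disagreement, acceptance or rejection). Kappa suits those. The Analysis plan works issue by issue and defines no total or dimension score, and phase 6 speaks of responses, so *scores* in phase 4 may be loose wording. This stands, and it makes the point conditional. Against it, alpha by dimension and factor analysis imply multi-item scales, and the Analysis plan expects quantitative as well as qualitative variables.

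A reader might also infer that sound items will be rated poor and then changed needlessly. The documents do not support that. No band is tied to a modification, phase 4 also yields results on content and comprehension, and the phase 6 retest follows the definitive version, so it cannot prompt a phase 5 change. Nor would a reported unweighted kappa be a wrong number: it correctly describes exact-category agreement, which is a different and stricter quantity than the stability of a score.

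**Conclusion.** The point holds as a conditional one of low severity. If any item is graded or any dimension or total score is tested for stability, the named measures understate its stability. Under equal-probability categories and correlations of 0.80 to 0.90, the shortfall against quadratic weighting is about 0.4 for 5 levels (0.75 − 0.33 = 0.42; 0.85 − 0.47 = 0.38) and about 0.6 for 11 levels (0.78 − 0.18 = 0.60; 0.88 − 0.27 = 0.61). The 11-level values are labelled poor across that range; the 5-level values lie on either side of 0.40. If every item is binary and no score is formed, or if kappa is already weighted and an index for scores is specified elsewhere, nothing is lost. The consequence is confined to questionnaire validation: a low value could inform the revision and would understate the reported stability. The main descriptive estimates are not directly affected.

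**What to change.** State the index by type of variable:

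- binary or nominal items: simple agreement and kappa, as now;
- ordinal items: quadratic-weighted kappa, with simple agreement beside it if wanted;
- any dimension or total score: an intraclass correlation, naming the form used.

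Give each with its 95% confidence interval, because 20 to 30 respondents locate a value only loosely within the bands. The existing bands can stay. If all items are binary and no score will be formed, one sentence saying so and the replacement of *scores* by *responses* in phase 4 would settle the point instead.

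The cost is analysis wording only: no extra respondents, items or fieldwork. For binary items the result is identical to the present plan.
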